## **Lay abstract**

Gabapentinoids (gabapentin and pregabalin) are antiepileptics that are frequently prescribed for multiple conditions associated with chronic pain. Current FDA and Health Canada approved indications include painful diabetic neuropathy, postherpetic neuralgia, fibromyalgia and neuropathic pain associated with spinal cord injury [1-4]. However, the majority of current prescriptions are for off-label indications, despite limited proven efficacy or evidence of lack of efficacy [5]. Side effects are common at recommended therapeutic doses and include lower extremity edema, drowsiness, increased risk of traumatic falls, as well as increased risk of death when co-prescribed with opioids [6, 7].

A previously published descriptive study has shown that gabapentinoid use is very common in medical inpatients (1 in 8 admissions) [8]. Only a minority of users (17%) present an approved indication. Many are taking the drug for reasons which have been disproven in randomized controlled trials. Furthermore, gabapentinoid users are more likely to be co-prescribed opioids, benzodiazepines or other sedative drugs which increases the risk of serious harm including death [6, 7].

Polypharmacy, defined as taking 5 or more medications, is extremely common in patients admitted to medical wards. Hospitalizations represent ideal opportunities to review with patients their medications, including initial indications, efficacy and side-effects, with identification of medications that should be appropriately discontinued, or "deprescribed". Unfortunately, attempts for deprescription of gabapentinoids are seldom made during hospital admissions to medical wards [8].

Different strategies exist to improve deprescription of potentially inappropriate medications during hospitalization. These include direct patient education through the distribution of patient-friendly brochures. These have been shown to lead to increased deprescription rates of sedative hypnotics up to 30 days post-discharge [9].

This trial will evaluate the impact of educational brochures, distributed to inpatients on medical wards, on deprescription rates of gabapentinoids. This intervention will be supplemented by brief information sessions for medical staff. This prospective controlled before-after trial will study the effectiveness of this combined intervention in five medical units, spread across two tertiary-care hospitals in Montréal, Canada.

## **Objectives of the research and relevance to safe medical care**

Gabapentinoid prescriptions have soared in North America over the past decade. In 2016, pregabalin (brand name Lyrica®) was the eighth medication in the United States with highest invoice spending, with 4.4 billion US dollars spent [10]. This surge in popularity is largely driven by rampant off-label use for various chronic pain conditions, such as osteoarthritis, chronic lower back pain, sciatica and cancer-associated pain [5]. Although there exists reasonable quality evidence to support the use of gabapentinoids for diabetic neuropathy and postherpetic neuralgia, there is currently no evidence or evidence of lack of efficacy for other indications, including various types of neuropathic pain [11-16]. However, in the face of the ongoing opioid crisis, physicians are turning to alternative analgesics, making gabapentinoids a popular choice.

Although serious adverse drug events are rare with gabapentinoids, side effects are common, especially at doses proven to be effective in clinical trials. Common symptoms include sedation, lower

extremity edema and traumatic falls in older adults [17, 18]. Gabapentinoid users are more likely to suffer from chronic cardiac, pulmonary and renal diseases, placing them at higher risk for adverse events [8]. The use of gabapentinoids for their analgesic effects leads to frequent co-prescription with opioids, which increases dramatically the risk of opioid-related death [6, 7]. Furthermore, there is growing concern about abuse and misuse of gabapentinoids, as symptoms of euphoria have been reported with supratherapeutic doses [19]. Several jurisdictions have changed the gabapentinoids to "controlled" status, treating them like narcotics and other drugs with abuse potential.

The common off-label use of gabapentinoids, for which there is no evidence to support efficacy, combined with the high potential for side effects, make this class of medication an ideal target for deprescription. Furthermore, most patients receive total daily doses inferior to those shown to be effective in clinical trials, which can be explained by poor tolerability of the drugs or decreased clearance from renal failure [8]. Unfortunately, deprescription rates of gabapentinoids are very low on medical wards [8].

Distribution of educational brochures to hospitalized patients has been shown to be effective in improving successful deprescription of potentially inappropriate medications [9]. The brochures are standardized 8 to 10-page letter size documents, written in a sixth-grade level vocabulary for ease of comprehension. Examples are available on the Canadian Deprescribing Network website. Specific documents exist for different classes of potentially inappropriate medications, such as sedative-hypnotics, opioids, gabapentinoids and proton pump inhibitors. They contain self-assessment tests on risks of medications, provide information on evidence of efficacy and common side effects, propose therapeutic alternatives and suggest tapering regimens in the form of illustrated calendars. Patients are clearly informed to contact their healthcare providers prior to discontinuing or tapering their medication. Distribution of these educational brochures during hospitalization in chronic sedative users lead to a discontinuation rate of 64% at 30 days post-discharge, versus 21% with usual care [9].

In this trial, we aim to demonstrate that distribution of educational brochures during hospitalization to chronic gabapentinoid users can lead to improvement of successful deprescription. We hope that the brochures will inform patients of the limited evidence to support use of gabapentinoids and the risks of common side effects, motivating them to attempt discontinuation. As clearly stipulated in the brochures, the patients are expected to reach out to a healthcare provider to discontinue the drug, as gabapentinoids need to be gradually tapered to prevent rebound seizures, even in the absence of an underlying seizure disorder. These healthcare providers can either be staff or residents on the medical ward at the time of hospitalization, or a family physician in the community after discharge. By improving deprescription of gabapentinoids, we hope to reduce off-label use and, consequently, unnecessary exposure to potential undesirable side effects, leading ultimately to improved quality of life.

## **Our primary objective is to facilitate the deprescription of gabapentinoids using a patient educational brochure.**

Specifically, we aim to:

1. **Primary outcome: evaluate the effectiveness of the patient empowerment intervention tool for deprescription of gabapentinoids in a hospital-based setting** as measured by the proportion of patient with a gabapentinoid prescription deprescribed (stopped or with an intent to taper to discontinuation) at 8-weeks post-hospital discharge.

This patient empowerment tool is a 10-page brochure based on social constructivist learning and self-efficacy theory. This will be paired with brief monthly orientation sessions for the medical staff and residents of the participating clinical teaching units during the intervention phase. These sessions will review the evidence for efficacy of gabapentinoids and introduce the use of educational pamphlets. Our primary endpoints will be sustained cessation of pre-hospital use at 8 weeks post-discharge. Discontinuation will be confirmed with consent to access to the *Dossier Santé Québec* (DSQ) and, as necessary to contact the respective community pharmacy of the participants.

## 2. Secondary outcomes:

- a. **Dose reduction (without intention to discontinue) measured at 8-weeks post hospital discharge**
- b. **Patient-centered outcomes (measured at 8-weeks post hospital discharge):**
  - i. changes in global functioning scores
  - ii. pain control
  - iii. cognition

These outcomes will be evaluated with the use of standardized questionnaires
- c. **Initiation of new pain medications at 8-weeks post-hospital discharge**
- d. **Increases in doses of current pain medications** because of gabapentinoid cessation measured at 8-weeks post hospital discharge

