## **Data collection**

Information about participants will be collected by the research assistants from the participants and their medical record. We will abstract reason for admission, comorbidities and other medications from the chart. At time of enrollment, we will obtain consent to directly obtain prescription history from the *Dossier Santé Québec* (DSQ), which is a prescription record database for all patients in Québec, as well as from the community pharmacy from which participants receive their medications. These will serve to validate deprescription. During the index admission, a first questionnaire will be administered in person and will collect information about demographics, including age, gender and residence style (independent, assisted living, etc.). We will also obtain a medication use history (for study drugs) and standardized questionnaires to assess global functioning, pain control and cognition. Follow up questionnaires will be administered at 8 weeks after hospital discharge by telephone. The follow-up questionnaire will collect any demographic changes such as destination of discharge and length of stay, will ask participants about deprescription (cessation, reduced use, intent to reduce, or no change), initiation or dose increase of other pain medications, occurrence of withdrawal symptoms, and finally will repeat the global functioning, pain control and cognition questionnaires.

Death will be determined from hospital records. Participants who are known to have died before 8 weeks post-discharge will be excluded from the analysis of the primary outcome (as they cannot attain it); however, they will be retained in the study for descriptive purposes and other outcomes.

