#### **2. Evaluate the effectiveness of a hospital-based deprescription intervention for unnecessary gabapentinoid prescriptions.**

Participants will be grouped by control and intervention based on the timing of the study. The primary outcome will be the complete cessation of gabapentinoid use or intent to taper to discontinuation (prescribed taper) measured at 8-weeks post hospital discharge. A secondary outcome will be measured as a dose reduction, without any intent to taper to discontinuation (decrease in medication use after

exposure to the intervention but no taper to complete cessation prescribed at the time of the 8-week study follow-up period).

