### Statistical analysis plan

We will use an "intention to treat" principle. We will analyze participant data according to their participation during the intervention or control period. For the primary outcome, we will perform a sensitivity analysis for patients who died or were lost to follow-up using the most recent available data on their gabapentinoid use (inpatient pharmacy records, discharge prescriptions or the provincial electronic medical record). We will assess binary outcomes using binomial regression comparing the intervention to no intervention and adjusting for age and sex. We will assess continuous outcomes (T scores) using linear regression comparing the intervention to no intervention, adjusting for baseline values, age and sex.

We will perform several preplanned subgroup analyses for the primary outcome, including an analysis of participants aged 80 or older; analyses based on reason for admission, discharge destination (community v. long-term care facility) and comorbidities; and an analysis looking at the effect of each study unit. Subgroup analyses will be treated as hypothesis generating and presented graphically with 95% confidence intervals.

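### Secondary outcome (d) counts pain-drug dose increases only when caused by gabapentinoid cessation, so it follows the cessation rate and cannot show whether overall analgesic escalation differs between periods

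*Protocol*

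**What the plan says.** **Outcome (d).** Protocol, section 2 *Secondary outcomes*, item (d) counts increases in current pain medication that arise "because of gabapentinoid cessation measured at 8-weeks post hospital discharge". Item (c), new pain medications, carries no such condition. Under item (b), pain control is measured whether or not the drug was stopped.

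**Data.** The *Data collection* section has the 8-week telephone questionnaire ask whether other pain medications were started or increased. It mentions no question about the reason. The *Blinding* section says outcomes were chosen, as far as possible, so that they need no individual judgement by the assessor.

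**Outcome (a).** This is listed as "Dose reduction (without intention to discontinue) measured at 8-weeks post hospital discharge". The data analysis section sets it beside the primary outcome (stopped, or a taper to zero prescribed) as a separate category. It describes a fall in use following "exposure to the intervention but no taper to complete cessation prescribed at the time of the 8-week study follow-up period".

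**Analysis.** The *Statistical analysis plan* section compares binary outcomes between periods by binomial regression adjusted for age and sex. It names no special denominator for (a) or (d). It also plans a primary-outcome subgroup by "discharge destination (community v. long-term care facility) and comorbidities", and labels all subgroups hypothesis generating.

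**The concern.** Outcome (d) is one of the two outcomes that bear on substitution: do patients whose gabapentinoid is withdrawn end up on more of something else? To answer that across the two periods, every participant must be able to have the event. Under the present wording only those stopping or tapering can, and the intervention is meant to enlarge exactly that group. A higher rate in the intervention period would then be expected from success on the primary outcome alone, and it would say nothing about total analgesic use.

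Outcome (a) has the reverse structure. Only those who do not meet the primary outcome can have it, so an effective intervention shrinks the group at risk. Read alone, a fall in dose reduction could pass for a failure.

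The discharge-destination subgroup is a lesser matter. Destination is settled after the brochure is handed out on the ward, so it is not a baseline characteristic.

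**Working it through.** **Inputs from the protocol** (*Justification of sample size*): control deprescription rate 13%; planned absolute increase 20 points, hence 33%; two-sided type 1 error 5%; type 2 error 20%; loss 15%; 80 per period.

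**The plan's own figure.** With mean rate 0.23, the pooled two-proportion formula gives

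n = [1.96·√(2·0.23·0.77) + 0.842·√(0.13·0.87 + 0.33·0.67)]² / 0.20² = 68.3, so 69 per period.

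Allowing for 15% loss gives 69/0.85 = 82, or 69 × 1.15 = 80. The stated 80 is reproduced to within two participants, so 13% and 33% are the rates the plan rests on.

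**Outcome (d).** Let q be the probability of an attributed dose increase among deprescribed participants, the same in both periods. The protocol gives no value for q, so a range is shown. Then P(d) = P(deprescribed) × q.

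| q (assumed) | Control 0.13q | Intervention 0.33q | Ratio |
|---|---|---|---|
| 10% | 1.3% | 3.3% | 2.54 |
| 20% | 2.6% | 6.6% | 2.54 |
| 30% | 3.9% | 9.9% | 2.54 |
| 50% | 6.5% | 16.5% | 2.54 |

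The ratio is 0.33/0.13 = 2.54 whatever q is. As a limiting case, suppose 20% of all participants in both periods have a dose increase, unrelated to stopping, and every increase in a deprescribed participant is attributed to stopping. Any-reason escalation is then 20% v 20%, while (d) reads 2.6% v 6.6%.

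With 80 per period, the power to detect these built-in differences is 13%, 23%, 32% and 51% for q of 10%, 20%, 30% and 50%. The shift would usually appear in the estimate and interval rather than as a significant test.

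**Outcome (a).** Let r be the probability of dose reduction among those not deprescribed, again equal in both periods and assumed. Then P(a) = P(not deprescribed) × r.

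| r (assumed) | Control 0.87r | Intervention 0.67r | Ratio |
|---|---|---|---|
| 10% | 8.7% | 6.7% | 0.77 |
| 30% | 26.1% | 20.1% | 0.77 |
| 50% | 43.5% | 33.5% | 0.77 |

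The ratio is 0.67/0.87 = 0.77. For (a) to show no difference, r would have to rise by 0.87/0.67 = 1.30, for example from 20% to 26%.

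**Discharge destination.** No arithmetic applies. The brochure is given in hospital; destination is recorded by the follow-up questionnaire. Residence type is recorded during the index admission.

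**The case against.** The best defence is that, with all participants in the denominator, (a) and (d) are true descriptions of what differed between the periods. More cessation-related dose increases would be a real consequence of the programme. That stands: the fault lies in what the outcomes can be taken to mean, not in the validity of the comparison. It does not rescue (d) as evidence on overall escalation.

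Several stronger readings are tempting, and the protocol does not support them.

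- *That (d) is the main harm outcome and substitution goes unmeasured.* The protocol does not rank (d) above the others. New pain medications and pain control are measured without any cessation condition.
- *That increases in participants who did not stop are never recorded.* The follow-up questionnaire asks about them. Only the definition of (d) leaves them out.
- *That the attribution is made unblinded.* The *Blinding* section rules out blinding participants and physicians but calls blinded outcome assessment critical, and nothing says who would attribute. What can be said is that control participants are not told gabapentinoids are the target, while intervention participants receive a brochure about them. Any reason given by the participant would therefore be differently informed in the two periods.
- *That (a) would make the intervention look harmful.* This needs (a) to be read apart from the primary outcome. If the control rate were 15% (an assumption), equal conditional rates give 15% × 0.77 = 11.6%, about 12 v 9 of 80, a gap this trial could hardly detect.
- *That the destination subgroup is distorted by the primary effect.* Nothing in the protocol links stopping the drug, or receiving the brochure, to where a patient is discharged, and the subgroup is only hypothesis generating. Destination may also be of interest in its own right, since some deprescribing is expected in the community.

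**Conclusion.** The point holds chiefly for (d). As worded, it is zero by construction in anyone not stopping or tapering, depends on a cause that the described data collection does not capture, and would differ 2.54-fold between periods at the planned 13% v 33% with no change in escalation among deprescribed participants. That ratio assumes that q is equal in both periods and that those able to have the event are those meeting the primary outcome. If only complete cessation counts, the group is smaller and the ratio becomes that of the complete-cessation rates, which the protocol does not give.

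For (a), the structural fall to 0.77 of control assumes equal r. The reference to exposure is a plain wording fault, because read literally no control participant could have the event.

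For the subgroup, only the general caution about a variable fixed after the intervention applies. The primary outcome and the sample size are unaffected throughout.

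**What to change.** 1. **Outcome (d):** define it as any dose increase of a non-gabapentinoid pain medication by week 8, in all participants and whatever the reason. Use the existing follow-up questionnaire item, supplemented by the provincial prescription record. The questionnaire should stay the lead source where available, since a prescription record may miss non-prescription analgesics. The record serves those who decline telephone follow-up.
2. **Outcome (a):** delete the reference to exposure and analyse one ordered outcome with all participants in the denominator: stopped or tapering to stop / reduced / no change (any gabapentinoid increase placed in this last level). State where the questionnaire's category for an intention to reduce belongs. Redefining (a) as any reduction including cessation is not advised, because it would largely restate the primary outcome. Nor is restricting (a) or (d) to non-stoppers or stoppers, which would select on an event after the intervention.
3. **Subgroup:** use residence type recorded at enrolment and keep discharge destination as descriptive.

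The cost is small: changes of wording, with no new variable and no change in sample size. The price is that (d) becomes less specific to cessation and picks up background dose changes.

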## Background

Gabapentinoids are a class of antiepileptic drugs which includes gabapentin (brand name Neurontin®) and pregabalin (brand name Lyrica®). The original gabapentinoid, gabapentin, was released in the 1990s for treatment of seizures, with pregabalin available a decade later for the same indication [5]. They both bind voltage-gated calcium channels in the central nervous system, inhibiting neuronal calcium influx and consequently release of excitatory neurotransmitters. This mechanism of action was felt to have potential analgesic properties for the treatment of neuropathic pain. Since their release, the FDA and Health Canada have approved the use of gabapentin and pregabalin for treatment of postherpetic neuralgia, with additional indications for pregabalin including painful diabetic neuropathy, fibromyalgia and neuropathic pain associated with spinal cord injury [1-4].

Despite a short list of approved indications, gabapentinoid prescriptions have soared in the past decade in both the United States and Canada [20, 21]. In 2016, Lyrica® was the eighth medication in the United States with highest invoice spending, with 4.4 billion US dollars spent [10]. The rise in gabapentinoid prescriptions has been largely driven by its new-found popularity for various off-label indications related to chronic pain, such as osteoarthritis, chronic lower back pain, sciatica and cancer-related pain [22]. Treating physicians have turned to gabapentinoids as a more acceptable therapeutic alternative to opioids. A Cochrane systematic review published in 2013 found reasonably good evidence for the use of both gabapentin and pregabalin for postherpetic neuralgia and painful diabetic neuropathy, while there was only evidence supporting pregabalin for the treatment of fibromyalgia and central neuropathic pain [16]. Numbers needed to treat varied from 4 to 10 for pain intensity reduction of at least 50% from baseline. However, benefits were compounded by a high risk of adverse events, leading to frequent drug discontinuation. Common side effects of gabapentinoids include sedation, dry mouth, lower extremity edema and traumatic falls in older adults [17, 18]. The poor tolerability of these medications at therapeutic doses might explain why up to half of users receive total daily doses inferior to FDA recommendations [8]. With regards to the treatment of other chronic pain conditions, including various types of neuropathic pain, there is either a lack of evidence or evidence of lack of efficacy to support the use of gabapentinoids [11-15].

There is a high prevalence of gabapentinoid use in patients admitted to medical wards [8]. The multiple comorbidities and rampant polypharmacy among these individuals place them at risk for adverse drug events, justifying careful screening for potentially inappropriate medications upon admission. A recently published retrospective descriptive study found that 1 in 8 patients admitted to a medical ward at a tertiary-care hospital in Montréal, Canada, between 2013 and 2017, was taking a gabapentinoid prior to admission [8]. Only a minority of users (17%) had a clear FDA-approved indication. The most common off-label indications included non-diabetic neuropathic pain (22%), musculoskeletal pain (16%) and cancer-associated pain (9%). Gabapentinoid users were more comorbid than non-users and were more

likely to be co-prescribed opioids (28% of users vs. 12% of non-users) and benzodiazepines (25% of users vs. 14% of non-users). This is very concerning in light of the evidence of increased opioid-related death with co-prescription of either gabapentin [7] or pregabalin [6].

The high prevalence of off-label use of gabapentinoids in comorbid patients who are vulnerable to their common side effects makes this class of drug an ideal target for deprescription. Deprescribing can be defined as the "systematic process of identifying and discontinuing drugs in instances in which existing or potential harms outweigh existing or potential benefits within the context of an individual patient's care goals, current level of functioning, life expectancy, values, and preferences" [23]. There exist many barriers for engagement of patients in deprescription, such as lack of support from a healthcare provider, misinformation regarding the risks and expected benefits of medications, perceived poor health, ongoing active medical issues and fear of withdrawal symptoms [24]. Barriers for physicians include prioritization of the management of acute medical illnesses over deprescribing, especially in an inpatient setting [25]. A reflection of this is the low deprescription rate of gabapentinoids in the previously mentioned study of medical inpatients, with only 13% of cessation or taper at discharge with intention to stop [8].

Multiple strategies exist to improve deprescription of potentially inappropriate medications. One promising method includes the use of direct patient education through the distribution of brochures [26]. These educational brochures contain self-assessments of knowledge of risks of medications, provide information pertaining to the evidence and potential harms of medications, present safer pharmacological and non-pharmacological alternatives for treatment and propose tapering regimens through the use of illustrated calendars, with instructions to contact a designated healthcare provider prior to discontinuing or tapering the medication. The goal of these pamphlets is to improve successful deprescription by promoting patient motivation and self-capacity, as well as soliciting opportunity for deprescription by encouraging patients to meet with their healthcare providers [24]. Specific brochures exist for different classes of drugs, such as benzodiazepines, opioids, gabapentinoids and proton pump inhibitors. Examples of brochures are available on the Canadian Deprescribing Network website at <https://www.deprescribingnetwork.ca/patient-handouts>. The distribution of brochures can take place in different contexts of patient care. In the EMPOWER trial (Eliminating Medications Through Patient Ownership of End Results), 303 community-dwelling older adults who were chronically taking benzodiazepines were randomly assigned to receiving either an educational brochure by mail or usual care [26]. At 6 months of follow-up, 27% of the intervention group had discontinued their benzodiazepine, versus 5% in the control group (number needed to treat 4).

The promising results of the EMPOWER trial inspired a subsequent study of sedative deprescription with the use educational brochures in medical inpatients [9]. Older adults admitted to a medical ward of a tertiary-care hospital in Montreal, Canada, were screened for chronic sedative use. A total of 50 patients received an educational brochure while hospitalized. At 30 days post-discharge, 64% of those patients had discontinued their sedative, which was significantly higher than the historical deprescription rate of 21% (number needed to treat 3). The higher deprescription rate associated with the intervention in this study (64%) compared to the EMPOWER trial (27%) illustrates the importance of seizing hospital admissions as an opportunity for deprescription. These events can drive patient motivation for change, particularly when presenting symptoms are related to side effects of the offending drug (for example, falls in a benzodiazepine user). Furthermore, the proximity of medical staff on the ward makes it easier for patients to discuss deprescription and initiate a tapering plan. Indeed, deprescription was shown to be more successful when initiated during hospitalization, rather than after discharge [9].

